### Data Management

Participants’ data are kept confidential according to our institutional regulations. Participants are identified by ID numbers, with all data stored and managed in REDCap in a secure, HIPAA (Health Insurance Portability and Accountability Act)-compliant server. Unanticipated problems and adverse events are recorded on electronic case report forms and reported to our institutional review board per regulations. As the study is no more than minimal risk, a data safety and monitoring board was deemed unnecessary.

### Sample Size

As this is a pilot feasibility study, a formal power calculation was not conducted. The sample size was determined based on the need to include a sufficient number of students exposed to the intervention, the availability of students in health classes at the participating public schools, and the timeframe allowed by school administrators. This approach allows us to assess our primary outcomes (eg, feasibility, acceptability, engagement, and satisfaction), as well as preliminary impact on relevant vaping-related constructs. We planned on including approximately 80 students in intervention classes and 40 students in control classes. This is based on an average of 25-35 students per class. We conservatively estimated that approximately 15%-20% of students will either not provide assent to be in this study or drop out post-assent. Therefore, we aimed to enroll approximately 150 participants.

### Analytic Plan

Data will be inspected for outliers, and descriptive analyses of baseline differences in sociodemographic and vaping-related characteristics between the VR group and the control group will be conducted using *t*-tests or chi-square tests, as applicable. We will examine differences in key baseline characteristics (eg, gender distribution between groups) so that they may be covaried in analyses. Feasibility, acceptability, engagement, and satisfaction (primary outcomes) in the VR group will be summarized as means and SDs for continuous variables, or number and proportion of participants for categorical variables, as appropriate. We will then report the number and proportion of participants who progressed through each of the 3 play sessions (chapters 1-10) of the VR game. Lastly, game ratings obtained after each play session will be reported as number and proportion of participants rating each category (“I liked it a lot,” “I liked it,” “meh,” or “thumbs down”).

Data on secondary outcomes will be summarized as means and SDs for continuous variables, or number and proportion of participants for categorical variables as appropriate, and compared between the VR group and the control group (baseline and follow-up). If low cell sizes occur, data might be aggregated to support statistical stability in the models. Differences in secondary outcomes between the groups will be evaluated by computing effect sizes (eg, Cohen *d* or odds ratio) as appropriate.

We will conduct analyses on treatment completers (the subsample of participants who completed the entire VR game) as well as intention-to-treat (as randomized). Additionally, we will perform analyses on the entire sample (English learners and English proficient students) as well as conduct analyses separately by English proficiency status. This will allow us to gain invaluable knowledge to inform future research regarding the feasibility of gamified health interventions for students with different levels of English proficiency.

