### Study Design and Random Assignment

Health education classes in the 2 high schools were randomized to either intervention (VR) or control (assessment only) by a statistician external to this study, using a 1:3 threshold probability. Three classes were randomized in 1 high school, and 4 classes in the other high school. Regarding the latter high school, 2 classes were “yoked” during randomization due to small class sizes. After completing a baseline survey, classes randomized to VR engage with the VR intervention once per week for 3-4 weeks, followed by a follow-up survey. Classes randomized to control complete baseline and follow-up surveys only, on the same schedule as the VR group. All study procedures take place during regular health classes. Students in control classes, as well as ineligible and nonassenting students in the VR classes, engage in alternative assignments regarding vaping or substance use from their respective teachers while study procedures are conducted. Only eligible participants who assented to be in this study completed pre- and post-assessments. As randomization occurs at the class level, teachers cannot be masked to the condition. Due to the nature of the intervention, study staff and participants were also not masked to the condition.

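### Covariates for the secondary-outcome comparisons may be chosen after looking at baseline differences between arms; a short list fixed in advance would handle chance imbalance better with about six randomised units

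*Protocol article*

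**What the plan says.** The Analytic Plan of the protocol article opens with a baseline comparison: "descriptive analyses of baseline differences in sociodemographic and vaping-related characteristics between the VR group and the control group will be conducted", by t-test or chi-square test. The next sentence links baseline differences to the choice of covariates: "We will examine differences in key baseline characteristics (eg, gender distribution between groups) so that they may be covaried in analyses". No threshold for a difference is given, and the list of key characteristics is open, with gender as the only example.

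Secondary outcomes are to be summarised and "compared between the VR group and the control group (baseline and follow-up"). The treatment contrast is then described as follows: "Differences in secondary outcomes between the groups will be evaluated by computing effect sizes", with Cohen d or an odds ratio as examples. Models are mentioned once, where sparse "data might be aggregated to support statistical stability in the models", but their terms are not given. Neither the baseline value of the outcome nor school is named as a term, and neither is excluded.

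Under Study Design and Random Assignment, the units are classes: "Three classes were randomized in 1 high school, and 4 classes in the other high school". In the second school two classes were yoked, so there are 3 + 3 = 6 independently allocated units.

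**The concern.** Choosing covariates by observed imbalance is a weak rule in any randomised trial, and weaker here for two reasons.

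- With about six units, the arms will usually differ by chance on something that predicts outcome.
- Student-level tests answer the wrong question. They ask whether an imbalance could be chance, which randomisation has already settled, and not whether the variable predicts the outcome. They also ignore the randomisation by class.

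An imbalance in a strong predictor can therefore pass as unremarkable and stay in the effect size, while a flagged difference in a weak predictor is adjusted for. The wording also leaves the choice open until the data have been seen.

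At stake are the secondary-outcome effect sizes. They are the trial's only randomised comparison and its only evidence on preliminary efficacy. There was no power calculation, so the estimates themselves are what the trial will offer on this aim.

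**Working it through.** **Inputs from the article.** 98 intervention and 52 control students recruited (Results); 7 classes, 2 of them yoked, in 2 schools (Study Design and Random Assignment). The article has no figure of its own on covariate adjustment to reproduce. Its enrolment target does reproduce: (80 + 40)/(1 − 0.20) = 150.

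**Inputs assumed, because the article gives none.** A 5% threshold for the baseline test; baseline-follow-up correlation ρ of 0.3 to 0.7; class-level intracluster correlation (ICC) of 0 to 0.10; school difference of 0.3 SD.

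**1. What a 5% screen lets through.** SE(d) = √(1/98 + 1/52) = 0.172. The largest non-significant observed difference is 1.976 × 0.1716 = 0.34 SD. For an underlying difference of 0.25 SD, the chance of a flag is about Φ(0.25/0.172 − 1.96) = Φ(−0.50) = 0.31. If it is missed, 0.6 × 0.25 = 0.15 SD stays in an unadjusted d at ρ = 0.6.

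**2. How much imbalance to expect.** SD of chance imbalance = √{[1 + (m − 1) × ICC] × (1/98 + 1/52)}, with m = 150/7 = 21.4 students per class:

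| ICC | Design effect | SD of imbalance |
|---|---|---|
| 0 | 1.00 | 0.17 |
| 0.05 | 2.02 | 0.24 |
| 0.10 | 3.04 | 0.30 |

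A difference of 0.25 SD is thus an ordinary result of this randomisation.

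**3. Precision at student level.** SE with baseline adjustment = 0.172 × √(1 − ρ²), which gives 0.164, 0.149, 0.137 and 0.123 for ρ = 0.3, 0.5, 0.6 and 0.7. That equals multiplying the sample by 1.10, 1.33, 1.56 and 1.96. These figures ignore clustering.

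**4. Simulation with clustering.** 4,000 runs per setting; 7 classes in 6 units, one control unit per school, no treatment effect, ICC 0.05, school difference 0.3 SD. Three estimators were compared:

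| | Unadjusted | Baseline adjusted only if p < 0.05 | Baseline and school fixed in advance |
|---|---|---|---|
| SD of estimate, ρ = 0.6 | 0.253 | 0.224 | 0.201 |
| SD of estimate, ρ = 0.3 | 0.253 | 0.246 | 0.242 |
| Slope on realised imbalance, ρ = 0.6 | 0.61 | 0.24 | about 0 |

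At ρ = 0.6 the selection rule leaves 0.24/0.61 = 39% of the dependence on imbalance in place. The fixed set has 1 − (0.201/0.224)² = 19% less variance than the selected one. At ρ = 0.3 the saving is 1 − (0.242/0.246)² = 3%. The mean error of all three estimators was within about 0.01 SD of zero. The baseline test gave p < 0.05 in about 17% of runs at ICC 0.05.

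**5. School alone.** With equal class sizes, the intervention share is 67% in one school and 75% or 50% in the other, depending on which unit is control. A school difference of 0.3 SD then shifts an unadjusted estimate by −0.03 or +0.05 SD. If the yoked classes together equal one class, the shift is about 0.

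**The case against.** The strongest reply is that this is a condensed article on a pilot. Model terms are commonly left to a fuller document, and only the selection sentence is fixed in print. That is right, and it limits the point to that sentence. Several stronger readings are tempting and are not supported:

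- **That the effect sizes omit baseline value and school.** The article is silent on both. It mentions models, and the baseline comparison covers vaping-related characteristics, so some baseline outcome values could enter as covariates.
- **That the plan is biased.** Averaged over randomisations, even the unadjusted estimate was centred correctly. The error is conditional on the imbalance that occurs, and the school contribution is small.
- **That a p < 0.05 gate applies.** The tests and the covariate sentence are adjacent, but no threshold links them. The 0.34 SD and 31% figures hold only if one is used.
- **That each outcome gets its own model.** The rule compares arms on baseline characteristics and could yield one covariate set for all outcomes.
- **That a false alarm is nearly certain.** This needs an assumed number of independent characteristics, which the article does not give. A flagged imbalance is also really present in the sample, and adjusting for it helps: selected adjustment did better than none.

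It is also true that the trial makes no claim to power, and that the primary outcomes are descriptive summaries in the intervention group, which this rule does not touch. Nor is a fixed set wholly free: in a cluster-level analysis of 6 units, a school term takes the residual degrees of freedom from 4 to 3 and the critical t value from 2.78 to 3.18, a factor of 3.18/2.78 = 1.14.

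None of this defends choosing covariates by observed difference. It bears on how much the choice matters.

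**Conclusion.** The point holds as a recommended improvement to a stated rule. Selecting covariates from observed baseline differences only partly removes the chance imbalance to be expected with about six units. At ICC 0.05 and ρ = 0.6 it leaves roughly 40% of the error due to imbalance, and the SD of the estimate is 0.224 against 0.201 for baseline and school fixed in advance. The plausible size of an individual miss is about 0.15 SD, for a 0.25 SD imbalance. At ρ = 0.3 the gain in precision is negligible.

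These sizes rest on assumed values for the correlation, ICC, school difference and 5% threshold. What does not rest on them is the direction: under the article's wording the covariate set depends on the data, and baseline values for most secondary outcomes are already available to do better.

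**What to change.** Replace the sentence on examining differences so that they may be covaried with a fixed set. Each between-arm effect on a secondary outcome is adjusted for the baseline value of the same outcome, where it was measured at baseline, and for school. Outcomes without a baseline counterpart, such as quit attempts since the programme started, are adjusted for school only. Any further covariate should be named before arms are compared on outcome, and the list must stay short.

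Report baseline characteristics descriptively by arm, and do not use tests to choose covariates.

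Apply the adjustment within whatever analysis allows for class clustering; covariates do not replace that allowance. If a cluster-level analysis is used, weigh the degree of freedom that school costs.

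The cost is analysis wording only: school is known and the baseline survey has been done. The article reports analysis as under way, so if outcome comparisons have begun, the new set should be labelled as a change to the published plan.

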**Conclusions:**

As VR is visual, auditory, and tactile, it is ideal for practicing skills, facilitating memory, and increasing the likelihood of transfer to real-world settings. The immersion of VR promotes engagement with the intervention, rather than external digital temptations. Our study is innovative due to the cluster-randomized design, focus on both prevention and cessation, integration of mood management, and implementation among racially and ethnically diverse teens. Incorporation into school-based health curricula allows for proactive reach.

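### Classes were randomised (7 classes, 2 yoked, so 6 independent units), but the analytic plan names only student-level methods for comparing the arms and takes no account of class or school

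*Protocol article*

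**What the plan says.** The Abstract (Conclusions) states: "Our study is innovative due to the cluster-randomized design". Study Design and Random Assignment gives the units: "Three classes were randomized in 1 high school, and 4 classes in the other high school". In the second school two classes were tied together "during randomization due to small class sizes", so they received one allocation between them. Allocation was done "using a 1:3 threshold probability". The number of classes per arm is not given, either overall or by school.

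Sample Size plans the arms in students: "We planned on including approximately 80 students in intervention classes and 40 students in control classes". Results reports 98 intervention and 52 control students.

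The Analytic Plan does three relevant things:

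- It compares the arms at baseline with t-tests or chi-square tests, and looks at key differences with a view to adjusting for them later.
- It summarises the primary outcomes (feasibility, acceptability, engagement, satisfaction) descriptively, in the VR group only.
- For secondary outcomes it states: "Differences in secondary outcomes between the groups will be evaluated by computing effect sizes", with Cohen d and the odds ratio as examples.

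Models are mentioned once, in connection with sparse cells, but none is specified. No confidence interval or hypothesis test is stated for any outcome.

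**The concern.** Students in one class share a teacher, a timetable and a peer group, so their answers on vaping and mood are likely to be correlated. When whole classes are allocated, the information about the arm difference comes from the six units and not from 150 separate students. A t-test or chi-square test on students assumes independence and understates the standard error. So does the usual interval for Cohen d or an odds ratio.

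Two uses are exposed. The baseline tests help to decide which covariates enter later analyses, so an inflated error rate would influence that choice. The secondary effect sizes serve the stated aim of assessing preliminary impact, and the Introduction hypothesises promising effects in the desired direction. Whether a pilot effect looks promising depends largely on its precision. If only two units are control, a difference between teachers or classes can easily pass for an effect of VR. A later class-randomised trial would also want an ICC, and the plan does not say one will be reported.

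**Working it through.** **Inputs from the document.** Classes: 3 + 4 = 7. Two are yoked, so the independent units number 3 + 3 = 6. Students: 98 VR and 52 control, 150 in total. Planned: 80 + 40 = 120, with an allowance that "approximately 15%-20% of students will either not provide assent to be in this study or drop out post-assent".

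**Assumptions.** ICC 0.01 to 0.10 (none is given). Units split 4 VR to 2 control (not stated; inferred from 98:52). Units of similar size, m = 150/6 = 25.

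**The plan's own figure.** 120/(1 − 0.20) = 150; at 15% loss, 120/0.85 = 141.2, that is 142. The target of about 150 reproduces at the upper end of the stated range. It contains no allowance for clustering, and the document says no power calculation was made.

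**Design effect.** DE = 1 + (m − 1) × ICC, and effective N = 150/DE.

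- ICC 0.01: 1 + 24 × 0.01 = 1.24; 150/1.24 = 121
- ICC 0.05: 1 + 24 × 0.05 = 2.20; 150/2.20 = 68
- ICC 0.10: 1 + 24 × 0.10 = 3.40; 150/3.40 = 44

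**Error rate of a student-level t-test.** Null trials were simulated with units of 25, 25, 24 and 24 against 26 and 26 (20,000 per setting).

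| ICC | Rejections at nominal 5% |
|---|---|
| 0 | 5.0% |
| 0.01 | 7.9% |
| 0.02 | 11.0% |
| 0.05 | 18.9% |
| 0.10 | 29.6% |

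Counting seven classes (5 against 2) instead of six units gives 7.7%, 10.9%, 18.4% and 28.4% at ICC 0.01, 0.02, 0.05 and 0.10, so the result does not hinge on the yoked pair.

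**Precision of Cohen d.** Treating students as independent, SE = √(1/98 + 1/52) = 0.172, and the 95% half-width is 1.96 × 0.172 = 0.34.

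By unit, SE = √{[ICC + (1 − ICC)/24.5]/4 + [ICC + (1 − ICC)/26]/2}, where 24.5 = 98/4 and 26 = 52/2. The degrees of freedom are 6 − 2 = 4, so t = 2.776.

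- ICC 0.01: √(0.01260 + 0.02404) = 0.191; half-width 0.53
- ICC 0.05: √(0.02219 + 0.04327) = 0.256; half-width 0.71
- ICC 0.10: √(0.03418 + 0.06731) = 0.3186; half-width 0.88

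Part of this widening comes from having only 4 degrees of freedom: at ICC 0 the half-width is already 2.776 × 0.172 = 0.48.

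**What it does to a reading.** Take an illustrative d of 0.40 at ICC 0.05. The student-level interval is 0.40 ± 0.34, or 0.06 to 0.74. The unit-level interval is 0.40 ± 0.71, or −0.31 to 1.11.

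**Allocation wording.** Read as a ratio, 1:3 puts 1/4 = 25% in control. Read as a one-in-three probability of control, it gives 33%. Planned: 40/120 = 33.3%. Recruited: 52/150 = 34.7%.

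**The case against.** The strongest reply is that the plan commits to very little that clustering could spoil. The t-tests and chi-square tests are stated for baseline only and are called descriptive. Cohen d and the odds ratio are point estimates, and clustering mainly affects their precision, for which no method is named. The unspecified models could carry a class term in a fuller plan that is not shown. The trial is a pilot, the comparisons are secondary, and the article says conclusions will be limited by small numbers and low power.

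Much of this stands, and it limits the point. A reader might infer that every interval and test in the trial is wrong. The document does not support that: it states no outcome interval or outcome test, and the primary outcomes are summaries within one arm.

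A reader might also infer that 1:3 contradicts the planned 80:40. It need not, because the one-in-three reading fits both 80:40 and 98:52, and student proportions need not match class-level probabilities when class sizes differ. The phrase is ambiguous, not contradictory.

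Nor does it follow that no valid 5% inference is possible. With 4 against 2 units a re-randomisation test cannot give a p-value below 1/15 (or 1/9 if one of three units per school is control), but nobody planned that test, and an interval using t on 4 degrees of freedom can exclude zero.

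What the reply does not remove is that the methods actually named for comparing the arms are student-level ones in a design the article itself presents as cluster-randomised. Low power is also a different matter from misstated precision. The Discussion lists small sample size and the lack of an attention control as limitations, but not clustering.

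**Conclusion.** The point holds in this limited form. The Analytic Plan does not reflect that six units were randomised. Its baseline tests, and any interval or p-value attached to the secondary effect sizes on a student-level footing, will be too optimistic if the ICC is above 0. At ICC 0 the student-level test keeps its level.

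The size depends on assumptions that the document cannot settle: the ICC range, the 4 against 2 split and the near-equal unit sizes. The direction does not depend on the exact values, and inflation is already visible at ICC 0.01. The primary feasibility, engagement and satisfaction summaries stand as planned. The article reports that analysis is still under way, so the change can be made before results are published.

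**What to change.** In the Analytic Plan:

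1. Describe baseline balance by arm without student-level significance tests, and name the adjustment covariates in advance.
2. Estimate secondary between-group effects by randomised unit. One option is to compare baseline-adjusted unit means, with the yoked pair as one unit and t on 4 degrees of freedom, or 3 once school is fitted. The other is a mixed model with a random class or unit effect, a fixed school effect and Satterthwaite or Kenward-Roger degrees of freedom.
3. Report d or the odds ratio with those cluster-adjusted intervals, and make no significance claims from student-level tests.
4. Report the ICC for each outcome, noting that six units estimate it very imprecisely.

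In Study Design and Random Assignment, state the number of units per arm in each school and say what the 1:3 threshold probability means.

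The cost is rewording and modest extra programming, with no new data provided the class identifiers are on file. The intervals will be visibly wider.

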### Ethical Considerations

The Boston University institutional review board approved the project on April 2, 2024 (IRB# 43102). Assent will be obtained from participants via REDCap, and parents will be sent an opt-out form, as per school protocol. Participants did not receive compensation for participation. All data will be deidentified, kept confidential, and stored in a secure location on an institutional server, which is backed up daily. Only certain members of this study’s staff or others designated by the principal investigator will have access to this study’s data. Protocol modifications will be reviewed and approved by our institutional review board and communicated to the American Heart Association.

## Results

The project institutional review board approved on April 2, 2024, and data collection began in April 2024 and ended in June 2024, and 150 participants were recruited (98 intervention and 52 control). Although freshmen and sophomore classes were targeted in this study, there were several juniors and seniors (n=5) in these classes due to school transfers and the need for them to take the mandatory curriculum. Data cleaning and analysis are underway, and results are expected to be submitted for publication in August 2025.

